### Outcomes

To analyze the effectiveness of IMT, several outcomes will be assessed. CF as main outcome, PIM, PEM, peripheral muscle strength, social support, anxiety, depression, coping with the disease, sexual dysfunction, QoL, sleep quality, eating habits, and body composition as secondary outcomes. The following sociodemographic and clinical variables will also be collected to characterize the sample and explore potential associations with the outcomes of interest: age, biological sex, marital status, educational level, profession, and nationality.

In the CRU consultation, an anamnesis will be performed in which the following data will be collected for the clinical history: cardiac comorbidities (revascularization, HF, heart valve surgery), presence of cardiovascular risk factors (current or previous smoking, arterial hypertension, dyslipidemia, diabetes mellitus, sedentary lifestyle, obstructive sleep apnea), locomotor, neurological, vascular, or respiratory comorbidities, physical exercise habits (type and time), and stratification of the patient's cardiac risk (low, medium, or high).

#### Sociodemographic outcomes.

Age will be recorded as a continuous variable in years, based on the participant's age at the time of data collection. Biological sex will be categorized as either male or female, based on the sex assigned at birth and recorded in official identification documents. Marital status will be classified into four categories: single, married, separated/divorced, and widowed. This variable reflects the participant’s current relationship and legal status. Educational level will be assessed based on the highest level of formal education completed by each participant. Categories included: no formal education, mandatory basic education, high school diploma or vocational training, university degree programs (bachelor's degree, diploma) and postgraduate studies (master's or doctorate). Nationality will be defined as the country of legal citizenship at the time of the study. This variable was used to assess the cultural and legal contexts of each participant.

Occupation will be categorized according to the participant’s current or most recent employment status and type of work, based on standard occupational classifications [24]. This included military; business and public administration management; technicians, scientists, and intellectuals; technical and support professionals; administrative employees; workers in catering, personal services, security and retail sales; skilled workers in agriculture and fisheries; craftsmen and skilled workers in manufacturing, construction, and mining, except plant and machine operators; skilled workers in the extractive industries, metallurgy, and construction; operators and assemblers of fixed installations and machinery; drivers and operators of mobile machinery; and unskilled workers.

#### Clinical outcomes.

Comorbidities will be recorded at baseline based on medically documented diagnoses of chronic conditions coexisting with primary health concerns. Before and after the intervention, the following assessments and evaluations will be performed.

To assess CF, simple ergometry will be performed following the clinical guidance by consensus of recommendations for clinical exercise tolerance testing according to The Professional Body for Cardiac Scientists [25], in which the maximum oxygen consumption (VO_2_max), duration of the test, and type of response will be measured. Ergometry, also known as a stress test, is a diagnostic technique that analyzes the response of the heart to exercise and quantifies the oxygen consumption of the individual performing the test. In this study, the exercise will be performed on a treadmill. The Bruce protocol, which progressively increases the speed of the treadmill and its inclination every 3 min, will be used. This procedure will be performed by a cardiologist in our unit. VO_2_max will be obtained in METS (a metabolic equivalent of task, 1 MET = 3.5 ml O_2_/kg/min). The time and type of response will be recorded. This may be clinically positive if the cardiologist appreciates the appearance of angina on exertion or is electrically positive if a horizontal or downward depression of the ST segment of 1 mm measured at 80 ms from the J point is present.

Left ventricular ejection fraction (LVEF) will be measured by a cardiologist using ultrasound, following the recommendations of the American Society of Echocardiography for use in clinical trials and in agreement with expert cardiologists [26].

The total number of sessions attended by each participant will be recorded at the end of the intervention period.

#### Strength measurements.

A MicroRPM® digital portable manometer (Vyaire Medical GmbH, Hoechberg, Germany) will be used to measure the MIP and MEP. These assessments will be performed according to the recommendations of the American Thoracic Society (ATS) [27] and the European Respiratory Society (ERS) [28] and following the protocol of the Spanish Society of Pneumology and Thoracic Surgery (SEPAR) [29]. MIP will be reassessed midway through the program (at the end of week 4) to readjust the training load.

Perypheral musculature will be assessed as follows. Maximum static quadriceps muscle strength will be measured with the patient seated on a stretcher and the knee flexed at 90° using a Hogan Health Industries model MicroFet 2 handheld dynamometer. Hand grip strength will be measured using a Jamar^Tm^ approved hydraulic dynamometer. The isometric strength of the hand and forearm muscles will be assessed with the arm extended along the body by performing a contraction for at least 3 seconds. The three maneuvers will be performed at least 20 seconds apart. The highest value obtained will be considered.

#### Questionnaires.

The level of physical activity will be assessed using the RAPA [30] (Rapid Assessment of Physical Activity) questionnaire validated in Spanish population [31]. The scale was designed to measure this variable in older adults. It consists of 9 items, seven of which seek to determine whether people comply with the recommendation to perform 30 minutes or more of moderate physical activity at least 5 days a week. The two additional items measure whether people perform flexibility and strength exercises. Based on the total score, it establishes the following categories of physical activity: “Sedentary,” “Not very active,” “Not very active regular light,” “Not very active regular” and “Active.”

To assess QoL, the SF-12 questionnaire version 2 (SF-12v2), translated into Spanish and validated in Catalonian population [32], will be administered. It measures two main components: physical health (PCS) and mental health (MSC). It consists of 12 questions, with 8 dimensions: general self-perception of health, physical capacity, physical functioning, emotional role, social functioning, mental health, physical pain and self-perception of vitality with options. It measures two main components, physical health (PCS) and mental health (MSC). The PCS and MCS scores are standardized on a scale from 0 to 100, where 50 is the mean for the general population. Higher scores indicate a better quality of life.

Anxiety and depression will be assessed using the Hospital Anxiety and Depression Scale (HADS), which is composed of 14 questions and divided into two subdimensions: anxiety (HADS-A) and depression (HADS-D) [33]. Each question has Likert-type responses, with scores ranging from 0 to 3. Thus, each subscale has a score ranging from 0 to 21 points. Scores between 0 and 7 indicate the absence of depression and/or anxiety, scores between 8 and 10 suggest a clinically significant disorder, and scores between 11 and 21 indicate the presence of moderate to severe depression and/or anxiety.

The Pittsburgh Sleep Quality Index (PSQI) [34] will be used to assess the participants’ sleep quality. It is the most widely used self-report questionnaire for this purpose in the literature. It consists of 19 self-assessed questions whose overall rating ranges from 0 to 21. Higher scores represent poorer sleep quality. Above 5 is considered a “bad sleeper” and below 5 a “good sleeper.” A change of 3 points is the minimum clinically significant difference.

The Duke scale [35] in its Spanish version [36] will be used to assess functional social support. It is a self-administered questionnaire with a Likert-type response scale (1–5). The score ranges from 11 to 55 points. The score obtained reflects perceived support rather than actual support. The lower score means less support. A score of 32 or more indicates widespread social support, whereas a score of less than 32 indicates low perceived social support.

To assess erectile dysfunction in male participants, the International Index of Erectile Function in its reduced version (IIEF-5) and validated in Spanish [37] will be used. It is a 5-question self-assessment questionnaire that addresses aspects such as confidence in achieving erections, rigidity of erections, ability to maintain an erection during sexual intercourse, and satisfaction with sexual activity. Each question is answered on a scale of 1–5, where 5 is the highest score and 1 is the lowest. The total score is obtained by adding the scores of each question, with a range of 5–25. It allows to classify erectile dysfunction as mild (17–21), moderate (12–16) or severe (5–11).

To determine female sexual dysfunction, participants will be given the Female Sexual Function Questionnaire [38]. This is a self-administered scale that assesses 10 domains of sexual activity. It consists of a total of 14 items, following a key question. Each domain comprises between 1 and 3 items. Each item is scored between 1 and 5. A score of 1 represents poor sexual function and a score of 5 represents normal or problem-free sexual function. The sum of the scores for the items in each domain is used to assess each domain.

To establish the severity of dyspnea, the scale created by the New York Heart Association (NYHA) [39] will be used. It reflects the patient's capacity for physical exertion and is therefore also called “NYHA functional class, which has four grades indicating greater dyspnea to a greater degree.

Eating habits will be evaluated using the Mediterranean diet adherence questionnaire [40]. It consists of 14 direct questions on the consumption of the main foods of the Mediterranean diet, such as olive oil, fruits, vegetables, legumes, fish, nuts, wine, and white meat. The scores are grouped into four categories: high adherence (12–14 points), medium adherence (8-11.99 points), low adherence (0-7.99 points).

#### Body composition and nutritional measurements.

Bioimpedance will be used to determine the body composition of the participants. The measurement will be made with an Akern bioimpedance meter (Nutrilab model). The body mass index (BMI) of each participant will be calculated after weighing and measuring them in the training room. Waist circumference will also be measured at the level of the navel with a tape measure. Nutritional ultrasound [41] will also be performed. The FujiFilm Sonosite SII ultrasound scanner will be used. The subcutaneous fat in the quadriceps without contraction, thickness of the rectus femoris muscle (anteroposterior distance), transverse diameter, area in cm^2^, and circumference will be measured. The thickness of the vastus intermedius will be measured (anteroposterior distance). In the abdomen without contraction, total subcutaneous fat, superficial subcutaneous fat, and pre-peritoneal fat will be measured.

### Sample size calculation

The sample size was calculated to detect differences between groups in our main outcome, CF, measured by VO_2_max. According to the meta-analysis by Fabero-Garrido et al [16], people with ischemic heart disease who have undergone an IMT program have a mean difference of 2.18 ml O_2_/kg/min with respect to the control group, and we want to find a deviation of 1 MET (3.5 ml O_2_/kg/min). The calculations were performed using the statistical software G*Power 3.1, considering a confidence level of 95% and a power of 80% in all cases.

Based on the above, a sample size of 33 subjects per group (66 in total) was determined. In addition, to minimize the impact of possible dropouts, the total sample was increased by 10% to 72 patients, which will lead to the final inclusion of 36 patients in each group.

### Allocation concealment

Consecutive sampling will be performed by a rehabilitation physician on patients attending the CRU consultation of HUVV who meet the criteria (see *Eligibility criteria* section) and sign the informed consent. Once included, each patient will be randomly assigned to either the intervention or control group (1:1 ratio) using a random sequence of numbers generated with the Simple Random Sampling module of Epidat 3.1 (open-access epidemiological analysis software developed by the Xunta de Galicia, Dirección Xeral de Saúde Pública). Specifically, to reach a sample size of n = 72, the software will generate a sequence that determines the group for each participant according to their order of enrollment. This simple random assignment will ensure maximum unpredictability in the assignment of participants, preventing any prediction of future assignments. These assignments will be generated in advance by an independent team member who will develop sequentially numbered, truly opaque, and sealed envelopes. Finally, the rehabilitation physician responsible for recruitment will open the corresponding envelope to reveal which group the participant belongs to.

### Blinding

Participants will receive instruction about IMT from one of the rehabilitation physicians, who will be different from the one performing the assessments. Furthermore, none of the participants will know to which group they belong, since all of them will be given the same IMT device, but with a different training load. The physiotherapist and nurse who will conduct the CRP training sessions will not be involved in the allocation of participants. The statistical analysis will be carried out by a statistician of the research team who will not participate in the allocation, assessment or intervention process. In addition, the participants’ data will be provided anonymously.

In the event of any adverse effect or circumstance that endangers the health of the participants, the researchers will be unblinded. If such a contingency arises, both a paper-based and an electronic record are always maintained and remain accessible to all authorized investigators.

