### Interventions

Both study groups will undergo 16 intervention sessions (2 times/week) of a CRP, consisting of multicomponent exercise (endurance and strength training), health education, and weekly group psychological therapy sessions. This program includes the core components of CRPs recommended by the American Heart Association and the American Association of Cardiovascular and Pulmonary Rehabilitation [12].

The CRP will be performed and supervised by the usual multidisciplinary team of the HUVV. The team is composed of a cardiologist, rehabilitation physician, endocrinologist, physiotherapist, nurse, and psychologist. The study participants will attend the CRU of the hospital three times per week. Two of these days will be dedicated to physical exercise sessions, and the third will be dedicated to health education and group psychological therapy sessions. The health education session will deal with a different topic each week (basic knowledge of their pathology, proper medication, safe physical exercise, sexual dysfunction, healthy eating, and control of cardiovascular risk factors). Subjects suffering from erectile dysfunction will be offered the possibility of being referred to a urologist. Participants with poorly controlled diabetes and/or morbid obesity will be referred to an endocrinologist on the CRU.

The training sessions will take place in the cardiac rehabilitation room at the HUVV in groups of 8 patients and will last approximately 75 minutes. This space has a rectangular floor plan, measures approximately 100m^2^, and is air-conditioned. It contains the equipment described in Table 1 for conducting exercise sessions, as well as telemetry equipment for monitoring participants during exercise. In addition, it has everything necessary to respond in the event of any adverse effects or cardiopulmonary arrest. This includes a stretcher, wheelchair, sphygmomanometer, stethoscope, electrocardiograph, and a fully equipped crash cart with a defibrillator.

**Table 1 pone.0343947.t001:** Structure of the cardiac rehabilitation exercise session.

Category	Description
Patient reception	Collection of constants (blood pressure, heart rate, and glycemia in case of diabetic patients), and placement of telemetry.
Warm-up	A battery of different full body exercises will be performed including diaphragmatic breathing, balance exercises, low load strength exercises and gentle endurance exercises.

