In addition to the classic CRP described above, the intervention group will undergo IMT during the same period. The Power Breath model – Medic Classic device will be used. The IMT will be performed by adjusting the device load to 70% of the MIP value measured prior to the start of the program. Participants will complete one daily training session four days a week (Monday, Wednesday, Friday, and Sunday), three sets of 10 repetitions, and a rest of 3-minutes between sets. The MIP value will be measured again halfway through the program to readjust the training load. Previous studies with patients with coronary artery disease have used training protocols that are similar in terms of workload, number of repetitions and sets, and distribution of weekly sessions. These clinical trials reported no adverse events, supporting the safety and tolerability of high-intensity IMT in this study population [22–24]. We hypothesize that high-intensity IMT training may lead to greater inspiratory muscle adaptations, resulting in improved CF and other outcomes compared to lower-intensity training [21–23].

The control group will be given the same device as the experimental group, but the load for all participants in the control group will be 5 cm of H_2_O. This load is so low that it cannot induce improvements in the inspiratory musculature. Therefore, it will act as a sham intervention in the control group.

A rehabilitation physician, with prior expertise and training in the practice of the device, will teach participants how to use it on the first day, and they will be instructed to do it individually at home. In order to prevent non-compliance with the IMT by the participants, they will be given a paper log to be filled in daily after the IMT session. At any time, participants may ask the rehabilitation physician who instructed them any questions they may have about using the device. During regular CRP exercise sessions, the physiotherapist will emphasize the importance of completing the prescribed IMT.

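### The identical device does not by itself assure participant blinding: the load can be felt, and patients probably from both arms meet in group sessions where IMT is raised

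*Protocol article*

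**What the plan says.** The Blinding section states that "none of the participants will know to which group they belong, since all of them will be given the same IMT device", and adds that the training load differs. It gives no other reason why participants stay blind. The trial is called triple-blind in the Abstract, Design and Conclusion, and triple blinding is listed as a strength under Strengths and limitations.

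The Interventions section describes the setting. "Both study groups will undergo 16 intervention sessions (2 times/week) of a CRP", and "The training sessions will take place in the cardiac rehabilitation room at the HUVV in groups of 8 patients". A third weekly visit holds health education and group psychological therapy. On the breathing training it says: "During regular CRP exercise sessions, the physiotherapist will emphasize the importance of completing the prescribed IMT". The training itself is not done in the session; participants are taught the device on day one and "they will be instructed to do it individually at home".

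The intervention load is set by "adjusting the device load to 70% of the MIP value measured prior to the start of the program". The paragraph on the intervention group continues: "The MIP value will be measured again halfway through the program to readjust the training load". The control load is a fixed 5 cm H2O in Interventions and 5% of MIP in the Abstract. Interventions describes the 5 cm H2O load as too low to train the inspiratory muscles.

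Under Allocation concealment, patients are assigned individually, 1:1, by simple randomisation in order of enrolment. The article does not say how the groups of 8 are formed or whether they are separated by arm.

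**The concern.** An identical device hides the arm only if the participant cannot tell the loads apart. Here the load is the whole difference between the arms. A participant with no reference point may not know whether the load felt is high or low, and this is what a same-device sham relies on. A conversation with another participant can supply that reference point, and the programme brings patients together twice a week for exercise and once for group visits, with IMT as a topic raised by staff. The mid-programme readjustment is a second possible cue: under Interventions it is described for the intervention group, whereas a fixed 5 cm H2O leaves nothing to readjust.

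The outcomes are open to this. The primary outcome comes from a treadmill test taken to maximum effort; Strengths and limitations calls it objective, but that does not remove its dependence on effort. MIP, MEP, quadriceps and grip strength also depend on effort. Anxiety, depression, quality of life, sleep, social support and sexual function are self-reported. Adherence to IMT rests on a paper diary, which the article itself recognises as open to bias, so a change in engagement after a participant learned the load could go unseen.

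**Working it through.** The plan gives no figure on blinding to reproduce. The check has three parts.

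**1. How likely is it that arms mix?**

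Inputs: 1:1 simple randomisation (Allocation concealment) and groups of 8 (Interventions). Assumption: groups form without regard to arm. The number k of trial patients in a group is not given, because the article does not say that groups hold trial patients only.

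Formula: P(both arms present) = 1 − 2 × 0.5^k. This equals 1 − 0.5^(k−1), the chance that a given participant shares a group with at least one participant of the other arm.

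- k = 2: 1 − 2 × 0.25 = 50%
- k = 3: 1 − 2 × 0.125 = 75%
- k = 4: 1 − 2 × 0.0625 = 87.5%
- k = 8: 1 − 2 × 0.0039 = 99.2%; with exactly 36 per arm, 1 − 2 × C(36,8)/C(72,8) = 99.5%

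Which k is realistic? Recruitment runs from 11 November 2024 to 31 December 2025, 415 days. With even recruitment of 72 patients and a programme of 56 days, about 72 × 56 / 415 = 9.7 trial patients are in the programme at once. They are spread over an unknown number of groups: five groups would give about 2 each, three groups about 3 each. The lower values of k therefore cannot be dismissed, and 99% is the upper end.

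**2. How different are the loads?**

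- With the Abstract's sham of 5% of MIP: 70 / 5 = 14-fold at any MIP.
- With the 5 cm H2O in Interventions, and an assumed MIP of 60 to 100 cm H2O (the article gives none): 0.70 × 60 = 42 and 0.70 × 100 = 70 cm H2O, so 42 / 5 = 8.4-fold to 70 / 5 = 14-fold.

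On either statement the contrast is large enough to be noticed if two participants compare. The two statements of the sham load contradict each other and must be reconciled, but the point here does not depend on which one stands.

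**3. What could a bias do? (illustration only)**

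The Sample size calculation gives 33 per group, 80% power and a target of 3.5 ml O2/kg/min (1 MET), but no SD. Solving a two-sided 5% two-sample t-test for 33 per group gives a standardised difference of 0.70, so SD = 3.5 / 0.70 = 5.0. With that assumed SD and no true effect, a bias in either direction would raise the two-sided 5% error rate as follows:

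- 0.1 MET (0.35 ml/kg/min): 5.9%
- 0.2 MET (0.70): 8.7%
- 0.3 MET (1.05): 13.4%
- 0.5 MET (1.75): 28.8%

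These are what-if values. The article gives no basis for choosing any of them.

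**The case against.** The same device at a low load is a real masking measure, and nothing suggests that participants are told their arm. IMT is done alone at home, so nobody sees another participant's device or breathing effort in the session. The physiotherapist's message concerns the prescribed training, which both arms have, so it reveals no allocation; nor does the text say that it is addressed to the whole group rather than to individuals. Unequal loads are expected even within the intervention arm, because each is set from the individual's MIP, so a difference between two patients does not prove that one has the sham. Whether participants know that one load is a sham depends on consent material that is not shown. Participant scripts, possibly with advice not to compare, may exist in operating procedures outside the article.

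Most of this stands, and it limits the point. A reader might infer that the arms are known to train together and that blinding has therefore failed. The documents do not support that. Mixing is an inference from individual allocation and unseparated groups, and the sessions give an opportunity for comparison, not evidence of it. A reader might also infer that any bias must favour IMT because sham patients would try less hard. That is not shown either: sham patients who learn of higher loads could compensate, which would pull the result towards no difference.

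The objection does not rescue the sentence in the Blinding section. That sentence draws a categorical conclusion from the device alone and in the same breath acknowledges that the load differs. This is a matter of what the article asserts, not of detail left to another document.

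**Conclusion.** The point holds in a limited form. The identical device does not assure that no participant will know the arm, because the loads differ about 8- to 14-fold (using an assumed MIP of 60 to 100 cm H2O where the sham is 5 cm H2O), the load can be felt, and participants meet repeatedly in sessions where IMT is mentioned. Arms probably mix: in 50% to 87.5% of groups with 2 to 4 trial patients and in 99% with 8, provided that groups form without regard to arm. The proportion of participants unblinded, and the size and direction of any bias, are unknown. No sample size or analysis figure changes. It is worth acting on because the safeguards cost almost nothing and the exposed outcomes include the primary one.

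**What to change.** - For participants still to start or still in the programme, instruct each one not to discuss load, effort or log with other patients.
- Give IMT reminders and log checks one to one rather than to the group, keeping the reminder as neutral to arm as it is now.
- Reword the Blinding section to say that participants are not told their arm and receive the same device, without asserting that none will know.
- Add possible participant unblinding, through the felt load and contact in group sessions, to the limitations under Strengths and limitations.
- Optionally, record at the end of the programme which load each participant believes they had and why, and report it descriptively by arm. Attach no decision rule: if IMT works, participants may guess correctly because they feel better, so guesses beyond chance would not show that masking failed.

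The cost is a few minutes of staff time per patient and some wording. The article reports recruitment as under way, with data collection expected to end by 31 March 2026, so the new instructions cannot help participants who have already finished; for them only the rewording and the limitation apply.
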